#### Data analysis

We will use an uncorrected χ^2^ statistic to test the null hypothesis for the proportion of patients developing lymphedema in the upper limb. These tests will be performed after 6, 12, and 24 months. We are interested in the course of the development of lymphedema, based on the measurements at each of the three specified time points. As development of lymphedema has been reported to occur 2 or more years after surgery, the measurement of lymphedema at 24 months is considered our primary endpoint.

To compare continuous data, such as pain and quality of life, analysis of covariance (ANCOVA) will be performed, using baseline values as a covariate. Separate analyses will be performed for the three time points (6, 12 and 24 months). The local recurrence rate in both groups will be analyzed by the Kaplan-Meier method and compared with the log-rank test. A repeated-measures analysis will be performed to compare the changes in continuous data between the two groups, until 2 years after treatment. It is expected that not only will the prevalence of lymphedema be higher in the standard ALND arm, but also that it will occur earlier and will be more severe. To test this hypothesis, interaction terms between treatment and time will be included in the repeated-measures analysis.

All data will be documented and analyzed using SPSS software (SPSS Inc., Chicago, IL, USA), with the exception of the repeated-measures analysis, for which SAS software (SAS Institute, Cary, NC, USA) with the procedure PROC MIXED. No interim analysis will be performed.

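### The treatment-by-time interaction is named as the test that lymphedema is earlier and more severe after standard ALND, but it tests only whether the group difference changes over time

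*Protocol article*

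**What the plan says.** All of this is in the Data analysis section of the protocol article.

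- **Prevalence.** An uncorrected chi-square is used "to test the null hypothesis for the proportion of patients developing lymphedema in the upper limb". On timing: "These tests will be performed after 6, 12, and 24 months". Of these, "the measurement of lymphedema at 24 months is considered our primary endpoint".
- **Continuous outcomes by visit.** ANCOVA with the baseline value as covariate, separately at each of the three visits. Pain and quality of life are given as examples; arm volume is not mentioned.
- **Continuous outcomes over time.** "A repeated-measures analysis will be performed to compare the changes in continuous data between the two groups, until 2 years after treatment". The software is SAS, "with the procedure PROC MIXED".
- **Course and severity.** Beyond higher prevalence after standard ALND, the authors expect of lymphedema "but also that it will occur earlier and will be more severe". The next sentence names the test: "To test this hypothesis, interaction terms between treatment and time will be included in the repeated-measures analysis".

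Table 1 notes that arm volume is also measured before surgery. The article does not say whether that measurement is a level of time in the mixed model or a covariate. It names no treatment effect or visit contrast from the model as the test of severity.

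**The concern.** Two claims are attached to one test. More severe is a statement about level: arm swelling is larger in one group at a visit, or on average. Earlier is a statement about when the groups separate. A treatment-by-time interaction addresses neither directly. Its null hypothesis is that the between-group difference is the same at every level of time.

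Two misreadings could follow. A sustained reduction in arm volume could be reported as a non-significant interaction and taken as no difference in severity. Conversely, a significant interaction could be presented as proof of earlier and more severe lymphedema, although opposite clinical courses produce it equally well.

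**Working it through.** **Inputs from the article.** 140 patients per group, alpha 0.05, power 0.8, lymphedema risk 15% against 5% (Sample size); visits at 6, 12 and 24 months, and arm volume also measured pre-operatively (outcome section, Table 1).

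**Assumptions not in the article.** Constant benefit of 40 ml in the inter-arm volume difference, SD 120 ml (standardized difference δ = 40/120 = 0.333), equal correlation ρ = 0.7 between any two measurements, no dropout. A range follows.

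**1. The plan's own figure.** With pooled variance, two-sided, no continuity correction:

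n = [1.960·√(2·0.10·0.90) + 0.842·√(0.15·0.85 + 0.05·0.95)]² / 0.10² = 140.1, rounded up to 141.

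Power at 140 per group is 0.7997. The stated 140 reproduces, and nothing below changes it.

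**2. Post-operative visits only, constant benefit.** Under equal correlation the interaction test has noncentrality

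λ = n / [2(1−ρ)] · Σ(dₜ − d̄)²,

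where dₜ is the standardized group difference at time t. With d = (δ, δ, δ) the sum is 0, so λ = 0 and the 2-df test rejects with probability alpha, 0.05, whatever the effect size or correlation.

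- 24-month contrast: λ = (n/2)·δ² = 70·0.1111 = 7.78 on 1 df, power 0.80.
- Average over visits: λ = 7.78 / [(1 + 2ρ)/3] = 7.78/0.8 = 9.72 on 1 df, power 0.88.

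**3. Pre-operative value as a fourth level of time.** Now d = (0, δ, δ, δ), the sum is 0.75·δ² = 0.0833, and λ = [140/(2·0.3)]·0.0833 = 19.4 on 3 df, power 0.97. At ρ = 0.3, λ = 8.33 and power is 0.67.

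**4. Opposite courses.** Compare a benefit of 40, 20, 0 ml (early, then gone) with 0, 20, 40 ml (absent early, then emerging).

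| Model | Early, then gone | Absent, then emerging |
|---|---|---|
| Post-operative only, λ = 12.96, 2 df | 0.91 | 0.91 |
| Pre-operative level included, λ = 17.8, 3 df | 0.96 | 0.96 |

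The results are identical in each row. The statistic depends on squared deviations, so reversing the sign of every difference also leaves it unchanged.

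**5. Range.** Over standardized constant differences of 0.30 to 0.50 and correlations of 0.3 to 0.8:

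| Test | Power |
|---|---|
| Interaction, post-operative visits only | 0.05 throughout |
| Interaction, pre-operative level included | 0.57 to above 0.99 |
| 24-month contrast | 0.71 to 0.99 |
| Average over visits | 0.77 to above 0.99 |

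A simulation of 4,000 trials at 0.35 SD and correlation 0.5 gave 0.048 (post-operative interaction), 0.868 (pre-operative level included) and 0.950 (average effect).

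**The case against.** Several points on the other side are sound.

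- **Prevalence is tested elsewhere.** The hypothesis sentence opens with prevalence, "It is expected that not only will the prevalence of lymphedema be higher in the standard ALND arm, but also that it will occur earlier", so a reader might infer that the plan would overlook a constant reduction in the rate of lymphedema. It would not: the chi-square test covers each visit, with 24 months primary.
- **Yes/no lymphedema is not put into a linear model.** A reader might infer this from the mention of PROC MIXED, but the article confines the repeated-measures analysis to continuous data.
- **The loss of power depends on coding.** The model is said to compare changes, and arm volume is measured before surgery. With the pre-operative value as a level of time, the interaction detects a constant post-operative benefit. It is therefore too strong to say that the planned test would miss one; that holds only for a model of post-operative visits.
- **ANCOVA may already cover severity.** Pain and quality of life are only examples. Applied to arm volume, the visit-wise ANCOVA would show a constant difference.
- **Detail may sit elsewhere.** A model containing the interaction also yields visit contrasts, and the full protocol or analysis plan may specify them.

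What these points do not remove is the explicit assignment. The article does not leave the test of timing and severity open; it names the interaction terms for it. Including the pre-operative level restores power but not interpretation, because the test remains unsigned and cannot tell early from late separation. The chi-square tests use a 200 ml cut-off and do not measure how severe the swelling is. ANCOVA on arm volume is possible but is not the analysis to which the article directs this hypothesis.

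**Conclusion.** The point holds for the secondary hypotheses of earlier and more severe lymphedema only. The named test does not match them. With post-operative visits alone its power for a constant benefit is 0.05, a result that needs no assumption about effect size or correlation. The comparison figures of about 0.80 (24-month contrast) and 0.88 (average effect) rest on the assumed 40 ml, SD 120 ml and correlation 0.7, with no dropout. With the pre-operative value as a level of time, power is about 0.97 on the same assumptions, but a significant result would still not establish direction, timing or severity.

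The documents do not support extending this to the primary analysis. The 24-month comparison of proportions and the 140 per group stand as they are.

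**What to change.** Reword the Data analysis section:

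1. **Severity.** From the planned mixed model, fit the inter-arm volume difference at 6, 12 and 24 months with the pre-operative difference as covariate. Name the treatment contrast at 24 months as the test, and report the average over visits alongside it. This also settles the role of the pre-operative value.
2. **Earlier.** Assess this from the 6 and 12 month contrasts of the same model, together with the chi-square tests already planned at those visits.
3. **Interaction.** Keep it only to describe whether the treatment effect changes over time.

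A discrete-time onset model, or a GEE or logistic mixed model for lymphedema over time, is optional and not needed for this fix.

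The cost is a change of wording, slightly more analysis work and a few more secondary contrasts. The measurements and the SAS software are already planned.

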## Discussion

Treatment of the axilla in patients with breast cancer has been a subject of recent debate. More than 50% of patients with a positive SLN appear to have no further LN involvement [20,21]. Based on these findings, the therapeutic role of cALND for these patients seems limited [22].

In the late 1990s, the American College of Surgeons Oncology Group (ACOSOG) Z0011 trial started in the USA. That trial randomized patients with breast cancer who had one to three positive SLNs to either cALND or a ‘wait and see’ policy. The results were recently published and no differences in overall survival (OS) or disease-free survival were seen after a median follow-up of 6.3 years [23]. Although the results do question the therapeutic benefit of ALND in SLNB-positive patients, abandoning ALND is not yet regarded as a standard of care. Moreover, considering the selected group of patients in the ACOSOG Z0011 trial, of which the majority received adjuvant chemotherapy and locoregional radiotherapy of the breast with inclusion of the lower regions of the axilla, the safety of omitting ALND in patients not fulfilling these criteria remains unclear.

A recently published study by Avril *et al*. [24] failed to show benefit in event-free survival and OS for post-menopausal patients with early breast cancer. This study randomized clinically node-negative post-menopausal patients with breast cancer to an ALND group or a no-ALND group. Adjuvant systemic therapy was based on the primary tumor characteristics.

In other studies, published several years ago, no difference was found in locoregional disease control, metastasis-free survival, and OS between patients treated with ALND and those treated with radiotherapy of the axilla [25]. However, as was the case with standard ALND, axillary radiotherapy appeared to be associated with an increased incidence of lymphedema [26,27].

The recently published Dutch guideline for breast-cancer treatment [28] gives several therapeutic options for the treatment of the axilla. It says that, in case of micrometastasis and macrometastasis with a maximum of two positive SLNs in patients receiving a breast-sparing therapy in combination with adjuvant systemic therapy, omission of the cALND can be considered. This may affect the accrual of the trial. However, there will be many patients left for whom pALND and cALND will remain the first-choice treatment; for example, in patients undergoing a mastectomy or in patients with a high risk of axillary involvement. For these patients, a limited and more tailored ALND based on the ARM technique might be a valuable tool to reduce the morbidity associated with the current ALND technique.

This multicenter randomized trial will provide evidence on whether or not upper-limb axillary LN preservation by means of ARM will decrease the side-effects of ALND.

## Trials status

This trial was designed in 2011 and 2012. The protocol passed through multiple amendments. Final approval from the medical ethics committee (METC) of Maxima Medisch Centrum, The Netherlands, was obtained on 21 September 2012 (METC number 1226: Centrale Commissie Mensgebonden Onderzoek (CCMO) number NL3920201512). This study will be carried out in compliance with the Helsinki Declaration. The trial is registered in the Dutch trial registration (TC 3698).

### Ethics

Patient recruitment will start in April 2013 in seven breast-cancer centers in the Netherlands. The study will finish enrolment as soon as 280 patients are included, and is expected to finish by April 2016. Collection and analysis of the results will be performed in the following 2 years.

## Abbreviations

ALND: Axillary lymph node dissection; ARM: Axillary reverse mapping; cALND: Complementary axillary lymph node dissection; CRF: Case report form; METC: Medical ethics review committee; pALND: Primary axillary lymph node dissection; PQ: Patient questionnaire; SLNB: Sentinel lymph node biopsy; WHOQOL: World Health Organization Quality of Life.
